#### Basic protocol

For eligible participants, sensors and transducers are attached for continuous monitoring of autonomic nervous system activity. Participants are asked to complete baseline questionnaire measures assessing relevant demographics and individual differences. After completing these questionnaires participants have a quiet period during which time they read neutral magazines. Following this "vanilla baseline" resting period (found to be effective in reducing effects of extraneous factors), a baseline measure of autonomic indices and the first saliva sample is obtained [70,71]. Consent for the experimental tasks and videotaping is then obtained, and the study physician subsequently administers a single dose of either 24 IU oxytocin or placebo intranasally (approximately 40 min before stress exposure). Following previous work in this area, a dose of 12 IU is sprayed into each nostril [39,72]. In the highly unlikely event of an adverse reaction during the conduct of the experiment, clear procedures have been set up to protect participants.

Task instructions for the stress tasks are given at this time. The stress tasks are initiated 40 minutes after oxytocin or placebo administration, the amount of time other studies have demonstrated it takes for oxytocin to act in the central nervous system [72]. Immediately prior to performing the task, a state mood measure and a second saliva sample are obtained. State mood and post-task measures and additional saliva samples are obtained after completion of the stress tasks. Autonomic function is monitored throughout the procedure. Prior research has strongly indicated that social-evaluative threat is strongest when an evaluative audience is present and the performance is being captured for permanent record [73]. Thus, video cameras mounted in the ceiling record participants' face and upper body during task preparation and performance. In addition to increasing levels of social-evaluative threat, the videotaping procedure also provides an additional method for assessing whether and how participants' responses to social stress varies across conditions; videotapes may be coded later for emotional responses during task conditions by raters blind to study hypotheses or experimental conditions.

At the completion of the protocol, the experimenter assesses whether the subject was suspicious about any aspect of the experiment, explains the nature of the study and debriefs the subject (and friend if present). Participants (and friends, if relevant) are then paid for participation. In summary, the experimental session follows standard procedure for social stress protocols, including a vanilla baseline, task preparation and performance period, and a recovery period. Components of the protocol that are unique to this study are uncomplicated - the administration of oxytocin or placebo prior to task preparation (~1 minute + quiet wait time for it to take effect), the presence of a supportive friend, and the brief screen at the start of the session (~20 minutes in most cases).

#### Oxytocin Manipulation

Building on research suggesting that intranasal administration of neuropeptides bypasses the bloodstream and achieves direct access to the brain [38], we administer intranasal oxytocin, using the biologically active form of the neuropeptide. Intranasal oxytocin has been widely prescribed in pregnant women to help induce labor and delivery, and in non-pregnant women to promote lactation. In non-pregnant women, intranasal oxytocin is typically self-administered by patients multiple times over the course of the day for several weeks at a time in a non-medical setting (e.g., in the patient's home prior to breast feeding) and is well tolerated. Experimental studies of effects of oxytocin have been conducted in men as well as women, with intranasal doses between 20 and 264 IU, and no adverse side effects have been reported [74-79]. Moreover, studies in humans on memory, affect, and biological parameters have clearly demonstrated behavioral and psychoneuroendocrine effects using a dose of 24 IU intranasal oxytocin (the dose we are using) [39,72,80-82]. No adverse or unanticipated side effects have been reported in these studies. While studies of intranasal oxytocin have largely focused on younger adults (ages 18 to 25), a number of studies have included older adults with and without mental health problems and reported no concerns around the use of intranasal oxytocin [79,83].

In this study, participants are randomly assigned to receive either oxytocin or placebo intranasally with both investigators and participants blind to condition. Participants assigned to the oxytocin condition receive a dose of 24 IU oxytocin and participants in the placebo condition receive saline. The Brigham and Women's Hospital Investigational Drug Pharmacy is responsible for obtaining the oxytocin and placebo and preparing them for administration to participants. For participants receiving oxytocin, aqueous oxytocin is inserted into a spray bottle. The spray bottle is calibrated so that emptying the spray bottle results in delivering 24 IU of oxytocin, with about half the bottle sprayed into each nostril. No dilution of the original aqueous form of the oxytocin is necessary. The nasal spray (oxytocin or placebo) is prepared within 24 hours of administration. Duration of drug administration is approximately 2-5 minutes.

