#### Manipulating Oxytocin

Manipulating oxytocin presents other challenges. When administered peripherally neuropeptides like oxytocin do not readily pass the blood-brain barrier and may also evoke potent hormone-like side effects. However, recent research has suggested that intranasal administration of neuropeptides can bypass the bloodstream and achieve direct access to the brain in both men and women [38]. Also, intranasal effects are more likely to be centrally mediated which mitigates concerns about the relevance of peripheral levels. An intranasal preparation of oxytocin is not commercially available in the U.S. at present which has made it difficult for U.S. investigators to pursue this line of research. Research by other investigators however, suggests that this is a promising line of work [36]. For example, Heinrichs and colleagues examined effects of social support and oxytocin under conditions of stress among healthy young men. Provision of social support and oxytocin each reduced cortisol response and distress in the men, and the combination of both social support and oxytocin had the strongest effects. Another study found intranasal administration of oxytocin increased trust among men [39]. Although baseline endogenous levels of oxytocin were not assessed, findings indicate that studies using intranasal administration of oxytocin may yield insight into the biological processes linking positive social interactions and health.

One concern for studies that look at effects of exogenously administered oxytocin is whether exogenous and endogenous effects are likely to be similar. Prior research suggests that endogenous and exogenous oxytocin have similar peripheral and central effects, including attenuation of behavioral and endocrine responses to stress [40-45]. Taken together, the research suggests that specific effects of oxytocin as an underlying biological mechanism linking socioemotional processes and health can be appropriately investigated using experimental methods with intranasal oxytocin administration [46].

To make it possible to pursue this line of research in the U.S., we have determined that the aqueous form of oxytocin which is commercially available in the U.S. (Oxytocin injection, USP, manufactured by American Pharmaceutical Partners, Inc.) can be used as a nasal spray. The FDA has concurred and they deemed our use of oxytocin injection exempt from requirements for an Investigational New Drug Application (IND).

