## Methods/Design

A placebo-controlled, double-blind design is employed. The key experimental manipulation involves the receipt of intranasal oxytocin spray versus placebo (saline) nasal spray. Social support (presence or absence) is also manipulated and age is measured as a continuous factor. Measures of estradiol levels are obtained. Primary outcomes are autonomic and neuroendocrine regulation and affective responses. Effects of oxytocin will be compared with effects of social support, as well as across gender and age. Within-gender group variation in effects of oxytocin will also be considered. This protocol has been approved by the Institutional Review Boards at the two institutions overseeing the research: Harvard School of Public Health and Brigham and Women's Hospital.

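### The active spray is the undiluted commercial injection and the placebo is saline rather than that product's vehicle, so the text secures neither the blind nor attribution to oxytocin alone

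*Protocol article*

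**What the plan says.** The active preparation is described in two places. In the Background, under Manipulating Oxytocin, the investigators explain that "the aqueous form of oxytocin which is commercially available in the U.S". (a product for injection) "can be used as a nasal spray". Under Oxytocin Manipulation this liquid goes into a spray bottle that delivers 24 IU when emptied, and "No dilution of the original aqueous form of the oxytocin is necessary".

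The comparator is also named twice. The opening of Methods/Design says "The key experimental manipulation involves the receipt of intranasal oxytocin spray versus placebo (saline) nasal spray", and Oxytocin Manipulation says "Participants assigned to the oxytocin condition receive a dose of 24 IU oxytocin and participants in the placebo condition receive saline". Neither place describes the placebo as the injection's vehicle, or as matched to the active spray in ingredients, smell, taste, appearance or volume.

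The article claims a double blind, "with both investigators and participants blind to condition", and makes a hospital investigational pharmacy "responsible for obtaining the oxytocin and placebo and preparing them for administration to participants".

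Methods/Design lists affective responses among the primary outcomes. Under Psychological Measures they are self-reported state scales, completed before the speech and after the arithmetic, both after dosing. The only end-of-session check described, at the end of Basic protocol, is that "the experimenter assesses whether the subject was suspicious about any aspect of the experiment".

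**The concern.** A placebo should differ from the active treatment only in the ingredient under test. Saline meets that standard for an undiluted pharmaceutical product only if the product is, apart from oxytocin, equivalent to saline. The article does not say that it is. If it is not, two things are at stake.

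The first is the blind. A spray into the nose can be tasted, smelled and felt. If the two liquids differ in those respects, some participants, or the physician who gives the spray, may form a view about the assignment. Self-reported anxiety, anger, depression, positive affect and perceived support are the outcomes most open to that.

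The second is attribution, and it does not depend on the blind. Potential Limitations states that oxytocin cannot be measured at baseline or after dosing, so the case that an effect is due to oxytocin rests wholly on the contrast between sprays. Any effect of another ingredient would be counted as an oxytocin effect, on autonomic and hormonal outcomes as well as on self-report.

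**Working it through.** No figure in the article depends on this point, so there is none to reproduce. The stated 80–90% power cannot be re-derived either, because no effect size, SD or reliability is given. The check is a comparison of statements, followed by an illustration.

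**Statements side by side**

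| Feature | Active | Placebo |
|---|---|---|
| Liquid | Commercial injection product (Manipulating Oxytocin) | Saline (Methods/Design; Oxytocin Manipulation) |
| Dilution | None (Oxytocin Manipulation) | Not applicable |
| Other ingredients | Not listed | Not listed beyond saline |
| Matching to the other spray | Not described | Not described |
| Prepared by | Investigational pharmacy | Same pharmacy |

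1. Because the active liquid is undiluted, whatever the product contains besides oxytocin reaches the nose.
2. The comparator is positively named as saline, twice. This is a stated design choice and not only an omitted detail.
3. The step from *different liquid* to *perceptibly or physiologically different spray* needs the product's composition, which the article does not give. Assumption: the injection contains at least one ingredient that saline lacks. If it contains none, the arms differ only by oxytocin and the concern largely falls away.
4. The closing question about suspicion could bring out a remark about the spray. It does not ask which spray the participant believes was given, so it is an insensitive check on the blind.

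**Illustration of sensitivity for self-report (assumed inputs)**

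Suppose there is no true effect, but a difference between the sprays shifts the mean self-report score by b SD between arms. For a two-group normal test with n per arm, the standard error in SD units is √(2/n), and the two-sided 5% test rejects with probability

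P(|Z + b/√(2/n)| > 1.96).

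The group size of 40 comes from Power and Sample Size and from Data Analyses. Forty per gender-by-drug group gives n = 2 × 40 = 80 per arm. Forty in each of the eight cells of the 2 × 2 × 2 design gives n = 4 × 40 = 160 per arm.

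- n = 80: √(2/80) = 0.158, so b = 0.1 gives 0.1/0.158 = 0.63.
- n = 160: √(2/160) = 0.112, so b = 0.1 gives 0.1/0.112 = 0.89.

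| Assumed b (SD) | Rejection rate, n = 80 | Rejection rate, n = 160 |
|---|---|---|
| 0 | 5% | 5% |
| 0.05 | 6% | 7% |
| 0.1 | 10% | 15% |
| 0.2 | 24% | 43% |
| 0.3 | 48% | 77% |

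The test is two-sided, so the rates are the same whichever way the shift goes. None of these values of b comes from the article. The table shows how sensitive the comparison would be to a shift, not that a shift exists.

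**The case against.** The strongest reply is that the decisive fact is missing. The article does not list the injection's contents and reports no taste, smell or sting. It describes intranasal oxytocin as well tolerated. A reader might infer that the sprays differ throughout their formulation and can be told apart; the text does not support that. This part of the reply stands, and it is why the point is conditional.

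A second reply is that matching is pharmacy detail, which an article leaves to the full protocol. This stands in part. Matching may be described there, and if so one sentence would settle the matter. But the article does not simply omit the comparator's composition: it says saline, twice.

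A third reply concerns direction. A reader might infer that any unblinding would favour the first hypothesis. Data Collection says participants do not know the hypotheses, and consent to possible oxytocin use is not shown to tell them that a calming effect is predicted. Each participant also receives one spray only and has nothing to compare it with. This stands: the direction cannot be claimed. It does not answer the attribution problem, which needs no expectation at all.

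Fourth, no outcome is described as rated by the study physician, so what the physician might notice is a weak route to bias. This also stands.

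Finally, a reader might infer that the closing interview could not reveal a failed blind. That is too strong, since an open question about suspicion may elicit comments on the spray.

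**Conclusion.** The concern holds in conditional form. As written, the comparator is saline and the active spray is an undiluted commercial product. Unless that product is equivalent to saline apart from oxytocin, the arms differ by more than oxytocin, and the text secures neither the blind for self-reported affect nor attribution of autonomic and hormonal effects to oxytocin alone.

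The conclusion rests on one assumption, that the injection contains an ingredient saline lacks. If it does not, the risk is small. The size and direction of any bias are unknown. The rejection rates of about 10% to 48% at 80 per arm, and 15% to 77% at 160 per arm, for shifts of 0.1 to 0.3 SD are illustrations and should not be read as estimates. The documents do not show that the blind failed or that results would be biased. The point is a cheap improvement to the design.

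**What to change.** 1. In Methods/Design and Oxytocin Manipulation, replace saline with a placebo that the investigational pharmacy prepares from the same non-active ingredients as the injection product, matched in volume and bottle. State the composition of both sprays. If the injection has no other ingredients than saline, saying so resolves the point.
2. In the closing interview described at the end of Basic protocol, before debriefing, add a forced-choice guess of the spray received, with a rating of certainty. Put the same question to the administering physician.
3. Report the guesses descriptively by arm. Do not use them to exclude participants: a guess is made after randomisation and may be affected by the drug, so removing confident correct guessers could itself introduce bias.

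The cost is some pharmacy compounding, notice to the two institutional review boards, and one or two questions in an interview already held. Guesses made after the tasks may partly reflect real drug effects, so they can support a judgement about the blind but cannot settle it.

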#### Social Support Manipulation

Support manipulations have varied across studies, with some studies requiring support providers to be in physical contact with participants [84,85] vs. activating support schemas [86], others asking support providers to give verbal support [66,87], use of confederates vs. friends to increase standardization of support provided [87-89] and various strategies employed to reduce potential for evaluation [85,90]. Findings generally suggest that reduced potential for evaluation, having a genuine relationship with the support provider, and verbal support are key components [56,57]. Building on prior work and our own pilot research, the social support condition is designed to standardize the support available to participants across individuals, as well as to maximize the effectiveness of the support provided. Prior to coming to the laboratory, participants are randomly assigned to one of two conditions, requiring them to appear alone or accompanied by a friend. They are then instructed to either bring a same-sex close friend (non-romantic, excluding spouses) with them, or to come alone. Same-sex friends are recruited to reduce variability associated with the meaning of their interactions. Upon arrival at the laboratory, individuals and their friends/support providers are introduced to the study and consented together. Friends then stay in a waiting room, and join participants at the start of the stress exposure when task instructions are given. All participants in the friend-present condition are told that the friend's role is to be "a support partner," and "to silently cheer him/her on." Friends sit where they can see the participant but not directly facing him or her. To control interaction between the participant and friend all remarks by the friend are scripted. Friends are asked to make an encouraging remark when they join participants and when participants finish each task. To minimize possible evaluation effects, friends are given their own tasks to complete (fill out questionnaires) and asked to wear a headset playing white noise during task performance. Friends are instructed not to distract participants at this time, but are given a stop watch and asked to nod and smile briefly at the subject at 1-minute intervals during each task. Friends leave participants at the start of the recovery.

#### Social Stress Manipulation

Social stress is induced using the Trier Social Stress Test (TSST), which prior work has suggested effectively creates a stressful situation that might be encountered in the real world [91]. The TSST generally requires participants to perform two separate tasks in front of an audience: a 5-minute public speaking task and a mental arithmetic exercise. Modifications have been made to ensure the effectiveness of the manipulation for all ages. For the speech task, participants are asked to prepare a speech about important self-relevant topics. All participants (regardless of age) are given the same 4 topics (Social Security reform, cost of prescription drugs, education reform, or the cost of gasoline) and asked to be prepared to present their thoughts about all the topics and potentially to answer questions about the topics from the evaluator. They are asked to try to talk for the full 5 minutes with as few pauses as possible. They are informed that the talk will be videotaped for later evaluation and that evaluators will be coding verbal and non-verbal behavior to assess their ability to successfully present their thoughts. They are further told that the evaluators have had extensive training on speech evaluation, are very skilled in assessing non-verbal behavior and body language, as well the persuasiveness and coherence of the speech. After the speech task, participants are asked to perform an arithmetic task, which is described as being related to mental ability and general intelligence. Participants are instructed to count backward from 996 by 7. Each time they make a mistake the evaluator informs them they have made an error and must start again. Participants are informed that they will be evaluated based on how many errors they make, how quickly they perform the task, and their overall presentation. As social support has been shown to be more beneficial when social threat is high [56], evaluators are trained to act in an impersonal fashion and to remind participants that they are being evaluated, to increase the social threat inherent in the task.

#### Biological Stress Responses

Multiple regulatory systems interact via a non-linear network to enable individuals to adapt to challenges and stressors in their environment. Exposure to acute stress elicits a cascade of cognitive, affective, and biological responses. Moreover, according to the biopsychosocial model cardiovascular responses may be either adaptive or maladaptive [92,93]. When situations are construed as threatening, cardiovascular responses show more vascular increases, as evidenced by increased ventricular contractility, heart rate, and total peripheral resistance with little change in cardiac output. When situations are construed more positively, cardiovascular patterns are also marked by increased ventricular contractility, heart rate, and cardiac output, but with decreases in total peripheral resistance. Cardiovascular responses consistent with more positive versus threatening appraisals have been linked with better outcomes -- lower anxiety, improved hormone functioning and higher telomerase activity -- and are considered more benign [94-96].

In a healthy or resilient system, a variety of regulatory mechanisms are maintained to counteract or speed recovery from stress-related activation. In a less resilient system, repeated and frequent activation of processes that are adaptive in the short-term may lead to cumulative systemic damage and ultimately initiate disease-related processes [97]. Vagal tone is hypothesized to be critically important in psychological and physical health. Porges (2003) argues that greater vagal control is associated with emotion regulatory capacity and possibly more positive social emotions and awareness of the social environment. Similarly, lower vagal tone has been related to depression, hostility, and anxiety [98-101]. Greater vagal control has also been associated with reduced risk of heart disease, relapse after myocardial infarctions, and reduced cellular aging [102-104]. If oxytocin and social support either directly increase vagal tone and physiologic resilience, or buffer the effects of stress, we might expect to see significantly more benign cardiovascular reactivity and higher levels of heart rate variability in response to a stressor and/or increased basal levels of parasympathetic tone. Each of these cardiovascular responses is measured over the course of the experiment.

Another index of regulatory capacity considers the neuroendocrine system. Previous work has found that the hormone cortisol (released by HPA axis activation) is highly reactive to stress, and chronically high levels of cortisol have been linked with risk for a variety of poor health outcomes including cardiovascular diseases and decreased immune functioning (although hypocortisolism has also been identified as problematic). Less studied but of growing interest, is the class of anabolic hormones which counter-regulate catabolic hormones and provide indications of physical and psychological thriving and greater adaptive coping [105]. One such anabolic hormone is DHEA and its active metabolite DHEA sulfate (DHEA-S), which is excreted by the zona reticularis of the adrenal cortex in response to adrenocorticotropic hormone (ACTH, part of the HPA axis cascade that directly precedes cortisol production). Epidemiological data has revealed relationships between low levels of DHEA and DHEA-S and cancer, age-related disorders, immune functioning, and also mental health outcomes, especially depression [106]. The ratio of anabolic to catabolic hormones provides additional information regarding the net anabolic vs. catabolic effect on the body, and is a more sensitive indicator of well-being than either measure alone. For example, androgens like DHEA can counter catabolic effects of cortisol on immune function, neurons, and on protein synthesis. The net ratio provides a measure called 'anabolic balance' (operationalized by DHEA/cortisol) [103,105,107]. This has been related to better performance, fewer depressive symptoms, and greater positive well-being [95,108]. We collect saliva at several points during the course of the experiment so that we can assess the effect of the experiment on hormonal response.

